**Since discharge from hospital . . .**

**Please record information about any medical assessments your child has had (family doctor or pediatrician, ED, hospital visit or admission):**

Date Provider Reason

________ ______________ ____________________________________________________________

________ ______________ ____________________________________________________________

________ ______________ ____________________________________________________________

**If you have seen your child’s family doctor or pediatrician, please describe any advice or help you have received regarding breastfeeding:**

*Date Description of advice or help*

________ ______________________________________________________________________________

________ ______________________________________________________________________________

________ ______________________________________________________________________________

**If you have sought advice or help regarding breastfeeding from someone else, please describe who you approached (private lactation consultant, public health nurse, public breastfeeding clinic, friend, family member, other) and the advice you received:**

*Source Description of advice or help*

________ ______________________________________________________________________________

________ ______________________________________________________________________________

________ ______________________________________________________________________________

**Other comments or information that you think might be relevant to the study:**

**Please complete when your child is 2 months of age:** __________________ (date)

**Please record the types and quantities of food sources your child has been given or is currently receiving (please check and complete all sections that apply):**

□ *Breast Milk*

□ Currently, my child feeds at the breast an average of ____ times per 24 hour period. Each feeding lasts approximately ____ minutes.

□ Currently, my child receives expressed breast milk ____ times per 24 hour period. Each feeding is approximately ____ mL or ____ ounces.

□ My child is exclusively breast fed (receives only breast milk).

□ I completely stopped breastfeeding on _________________ (date)

□ *Formula*

□ I introduced my baby to formula on ________________ (date)

□ Currently, my child receives formula an average of ____ times per 24 hour period. Each feeding is approximately ____ mL or ____ ounces.

□ I stopped all formula on _________________ (date)

□ *Other milk (cow’s milk, soy milk, rice milk, goat’s milk, etc.)*

□ I introduced my baby to other milk on ________________ (date)

□ Currently, my child receives other milk an average of ____ times per 24 hour period. Each feeding is approximately ____ mL or ____ ounces.

□ I stopped all other milk on _________________ (date)

□ *Solids (pabulum, cereals, other prepared foods)*

□ I introduced my baby to solids on ________________ (date)

□ Currently, my child receives solids an average of ____ times per 24 hour period.

□ I stopped all solids on _________________ (date)

**Since you last recorded in this book . . .**

**Please record information about any medical assessments your child has had (family doctor or pediatrician, ED, hospital visit or admission):**

Date Provider Reason

________ ______________ ____________________________________________________________

________ ______________ ____________________________________________________________

________ ______________ ____________________________________________________________

**If you have seen your child’s family doctor or pediatrician, please describe any advice or help you have received regarding breastfeeding:**

*Date Description of advice or help*

________ ______________________________________________________________________________

________ ______________________________________________________________________________

________ ______________________________________________________________________________

**If you have sought advice or help regarding breastfeeding from someone else, please describe who you approached (private lactation consultant, public health nurse, public breastfeeding clinic, friend, family member, other) and the advice you received:**

*Source Description of advice or help*

________ ______________________________________________________________________________

________ ______________________________________________________________________________

________ ______________________________________________________________________________

**Other comments or information that you think might be relevant to the study:**

**Please complete when your child is 4 months of age:** __________________ (date)

**Please record the types and quantities of food sources your child has been given or is currently receiving (please check and complete all sections that apply):**

□ *Breast Milk*

□ Currently, my child feeds at the breast an average of ____ times per 24 hour period. Each feeding lasts approximately ____ minutes.

□ Currently, my child receives expressed breast milk ____ times per 24 hour period. Each feeding is approximately ____ mL or ____ ounces.

□ My child is exclusively breast fed (receives only breast milk).

□ I completely stopped breastfeeding on _________________ (date)

□ *Formula*

□ I introduced my baby to formula on ________________ (date)

□ Currently, my child receives formula an average of ____ times per 24 hour period. Each feeding is approximately ____ mL or ____ ounces.

□ I stopped all formula on _________________ (date)

□ *Other milk (cow’s milk, soy milk, rice milk, goat’s milk, etc.)*

□ I introduced my baby to other milk on ________________ (date)

□ Currently, my child receives other milk an average of ____ times per 24 hour period. Each feeding is approximately ____ mL or ____ ounces.

□ I stopped all other milk on _________________ (date)

□ *Solids (pabulum, cereals, other prepared foods)*

□ I introduced my baby to solids on ________________ (date)

□ Currently, my child receives solids an average of ____ times per 24 hour period.

□ I stopped all solids on _________________ (date)

**Since you last recorded in this book . . .**

**Please record information about any medical assessments your child has had (family doctor or pediatrician, ED, hospital visit or admission):**

Date Provider Reason

________ ______________ ____________________________________________________________

________ ______________ ____________________________________________________________

________ ______________ ____________________________________________________________

**If you have seen your child’s family doctor or pediatrician, please describe any advice or help you have received regarding breastfeeding:**

*Date Description of advice or help*

________ ______________________________________________________________________________

________ ______________________________________________________________________________

________ ______________________________________________________________________________

**If you have sought advice or help regarding breastfeeding from someone else, please describe who you approached (private lactation consultant, public health nurse, public breastfeeding clinic, friend, family member, other) and the advice you received:**

*Source Description of advice or help*

________ ______________________________________________________________________________

________ ______________________________________________________________________________

________ ______________________________________________________________________________

**Other comments or information that you think might be relevant to the study:**

**Please complete when your child is 6 months of age:** __________________ (date)

**Please record the types and quantities of food sources your child has been given or is currently receiving (please check and complete all sections that apply):**

□ *Breast Milk*

□ Currently, my child feeds at the breast an average of ____ times per 24 hour period. Each feeding lasts approximately ____ minutes.

□ Currently, my child receives expressed breast milk ____ times per 24 hour period. Each feeding is approximately ____ mL or ____ ounces.

□ My child is exclusively breast fed (receives only breast milk).

□ I completely stopped breastfeeding on _________________ (date)

□ *Formula*

□ I introduced my baby to formula on ________________ (date)

□ Currently, my child receives formula an average of ____ times per 24 hour period. Each feeding is approximately ____ mL or ____ ounces.

□ I stopped all formula on _________________ (date)

□ *Other milk (cow’s milk, soy milk, rice milk, goat’s milk, etc.)*

□ I introduced my baby to other milk on ________________ (date)

□ Currently, my child receives other milk an average of ____ times per 24 hour period. Each feeding is approximately ____ mL or ____ ounces.

□ I stopped all other milk on _________________ (date)

□ *Solids (pabulum, cereals, other prepared foods)*

□ I introduced my baby to solids on ________________ (date)

□ Currently, my child receives solids an average of ____ times per 24 hour period.

□ I stopped all solids on _________________ (date)

**Since you last recorded in this book . . .**

**Please record information about any medical assessments your child has had (family doctor or pediatrician, ED, hospital visit or admission):**

Date Provider Reason

________ ______________ ____________________________________________________________

________ ______________ ____________________________________________________________

________ ______________ ____________________________________________________________

**If you have seen your child’s family doctor or pediatrician, please describe any advice or help you have received regarding breastfeeding:**

*Date Description of advice or help*

________ ______________________________________________________________________________

________ ______________________________________________________________________________

________ ______________________________________________________________________________

**If you have sought advice or help regarding breastfeeding from someone else, please describe who you approached (private lactation consultant, public health nurse, public breastfeeding clinic, friend, family member, other) and the advice you received:**

*Source Description of advice or help*

________ ______________________________________________________________________________

________ ______________________________________________________________________________

________ ______________________________________________________________________________

**Other comments or information that you think might be relevant to the study:**

____________________________________________________________________________________________

____________________________________________________________________________________________

__________________________________________________________________

**Appendix 5**

**Nomogram for treatment of hyperbilirubinemia**

**Appendix 6**

**Data collection form**

**Patient Study Number:______________**

Language most comfortable with:

English

French

Mother’s age

Mother’s education level

Elementary school / some high school

Completed high school

Vocational / technical training (post high school)

Some university training

Completed university

Household income

Under 30 000$

From 30 000$ to 70 000$

From 70 000$ to 100 000$

Above 100 000$

Declined to answer

Maternal smoking at home

Yes

No

If yes, how much?

Does anyone else smoke at home?

Yes

No

Mother’s marital status

Married / common-law

Single

How many children prior to patient?

How many breastfed children prior to patient?

Did you seek breastfeeding support with these infants?

Who followed the pregnancy?

Obstetrician

Family physician

Midwife

Other (specify)

No prenatal care

Attendance at prenatal classes?

Yes

No

Will mother go back to work before child is one?

Yes

No

If yes, when?

Baby’s age at admission to CHEO?

Baby’s birth weight?

Gestational age at birth?

Baby’s weight on admission to CHEO?

Baby’s weight on discharge from CHEO?

Urine culture done?

Yes

No

Blood culture done?

Yes

No

Cerebrospinal fluid culture done?

Yes

No

Antibiotic therapy given?

Yes

No

Intravenous fluids given?

Yes

No

Duration & volume of fluid given before weaned off

Duration of phototherapy in hours

Length of hospital stay in days

Need for formula supplementation while in hospital?

Yes

No

Formula given prior to hospitalization?

Yes

No

**Appendix 7**

**Qualitative Interview for the Intervention Group**

**After the intervention:**

We want to understand your experiences working with the CHEO lactation consultant during your hospital stay and during the follow-up sessions. Please describe how you felt about breast feeding prior to meeting with the lactation consultant, and any concerns or specific questions about breastfeeding that you hoped to have answered.

Please describe how you felt during the meeting. Was the encounter a positive experience?

Please explain which aspects of the first meeting in hospital you found helpful, versus those that you felt were not helpful. Was there one component that you felt was most helpful?

Please describe how you felt after the first session. Were your concerns and questioned addressed?

Please explain which aspects of the follow-up sessions you found helpful, versus those that you felt were not helpful. Was there one component that you felt was most helpful?

Please share your thoughts on the number and frequency of the follow-up sessions.

Please describe how you felt when your child was admitted, and when he/she was discharged from the hospital.

Please describe how confident you felt with your breastfeeding skills and what else could have been done at CHEO to help you.

If this intervention were to be used as a model for a breastfeeding support program at CHEO for all mothers, what recommendations would you have?

**At the end of the study period:**

We want to understand your experiences working with the CHEO lactation consultant during your hospital stay and during the follow-up sessions.

When we spoke last, you seemed to feel that X was the most useful component of the intervention. Now that some time has passed, is this still how you feel?

Now that some time has passed, do you have other recommendations to make, should this intervention be used as a model for a breastfeeding support program at CHEO for all mothers?

If you needed additional help with breastfeeding after the meetings with the lactation consultant were over, please describe how you addressed your need.

If you discontinued breastfeeding after your child’s admission to the hospital, please describe if anything could have been done differently at CHEO to help you continue.

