Feedback on the intervention will be obtained via semi-structured phone interviews. Twenty women from the intervention group will be randomly selected. Consent to contact the mothers for the purpose of these interviews will have been obtained on the original consent form signed at enrollment. A first set of phone interviews will occur at the end of the intervention period (after the 3 follow-up sessions with the lactation consultant are completed), and at the end of the study period (after the 6 month follow-up period). The interview tool (see Appendix 7) will elicit information on the participants’ perceptions of the intervention. More specifically, what they found most and least helpful, and what changes they would like to see if a breastfeeding support program were to be implemented at the hospital.

Semi-structured phone interviews will also be conducted with women from the control group to gather information on their experience at CHEO, and to determine whether they believe they received adequate support with breastfeeding (see Appendix 8). Twenty women from the control group will be randomly selected for interviews. Consent to contact the mothers for the purpose of these interviews will have been obtained on the original consent form signed at enrollment. A first set of phone interviews will occur one week after hospital discharge, and at the end of the study period (after the 6 month follow-up period).The semi-structured interviews will be conducted for both groups by the first research assistant, as that person will not be blinded to group allocation as he / she will be the person contacting the lactation consultant for mothers allocated to the intervention group.

At the end of the study period, an International Board Certified Lactation Consultant, independent of the study, will be asked to review 10% of the files kept by the study lactation consultant to ensure that advice provided to women met standard of care, as defined by the International Board of Lactation Consultants.

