**At the end of the study period:**

We want to understand your experiences after your child was discharged from CHEO.

When we spoke last, you seemed to feel “a certain way X” about your breastfeeding skills. Now that some time has passed, is this still how you feel?

Do you feel your breastfeeding needs were addressed adequately when you were at CHEO? What else could have been done to help you.

If you needed additional help with breastfeeding after you were discharged from the hospital, please describe how you addressed your need.

If you discontinued breastfeeding after your child’s admission to the hospital, please describe if anything could have been done differently at CHEO to help you continue.

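### One item in each six-month interview script feeds the mother's earlier view back to her before any open question, so agreement on that item cannot be told apart from acquiescence

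*Protocol*

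**What the plan says.** Section 4.7 of the Protocol plans two rounds of semi-structured telephone interviews with 20 randomly selected mothers in each arm. Intervention mothers are interviewed after the last follow-up session and again when the six-month follow-up ends. Control mothers are interviewed a week after discharge and again at the end. For the intervention group, the tool is meant to draw out "what they found most and least helpful, and what changes they would like to see" if a hospital programme were set up.

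The first-round script in Appendix 7 asks openly about helpful and unhelpful aspects, once for the hospital meeting and once for the follow-up sessions. Each time it adds "Was there one component that you felt was most helpful".

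The six-month script in Appendix 7 replaces these questions with one item. It states "When we spoke last, you seemed to feel that X was the most useful component of the intervention" and asks "Now that some time has passed, is this still how you feel".

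The six-month script in Appendix 8 opens in the same way on a different topic: "When we spoke last, you seemed to feel “a certain way X” about your breastfeeding skills", followed by the same closed question.

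Section 5.3 plans inductive thematic analysis of the transcripts.

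**The concern.** A question that supplies the answer and asks for confirmation invites agreement. Because the item comes before any open question, the mother has no chance to say what she thinks now before hearing what she is understood to have thought then. If she agrees, the transcript does not show whether her view is stable or she simply accepted the summary.

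At stake is the use made of the second round. The intervention interviews are meant to inform what a hospital breastfeeding programme should contain. If a component named in the first round recurs at six months only because the interviewer named it, a thematic analysis could read the recurrence as support. In the control arm the affected topic is confidence in breastfeeding. The Protocol's background (sections 2.3 and 2.4) treats maternal confidence as a strong predictor of how long breastfeeding lasts, so an unprompted reading of it is worth having.

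**Working it through.** No arithmetic beyond a count applies, since the point concerns the wording and order of the scripts. The check sets the two rounds side by side.

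**Intervention group (Appendix 7)**

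| Topic | First round | Six months |
| --- | --- | --- |
| Most helpful | Asked openly, twice (hospital meeting; follow-up sessions) | Earlier answer stated, then a closed question |
| Least helpful | Asked openly, twice | Not asked |
| Recommendations | Asked openly | "Now that some time has passed, do you have other recommendations to make" |
| Later help with breastfeeding | Not asked | "If you needed additional help with breastfeeding after the meetings with the lactation consultant were over, please describe how you addressed your need" |
| If breastfeeding stopped | Not asked | Open question on what could have been done differently |

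Three things follow.

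1. One of the four six-month prompts restates an earlier answer. It is the only one about helpfulness, and it comes first.
2. X is not determined by the first round. A mother asked twice for the most helpful component may name two, one or none, yet the six-month item has room for one. The interviewer has to choose, and the tentative phrasing of the item makes X the interviewer's reading of what was said.
3. The other three prompts quote no earlier answer. The recommendations prompt asks for additions to what was said before, so it is loosely tied to the first round, but it does not tell the mother what she said.

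**Control group (Appendix 8)**

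In the first round the mother is asked openly how confident she felt about her skills. At six months her earlier feeling is stated and the closed question follows. Again this is one of four prompts. The other three (whether her needs were met and what else could have helped; how she obtained later help; what could have been done differently if she stopped) do not restate an earlier answer.

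**Extent**

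Twenty mothers in each of two arms gives 20 × 2 = 40 planned six-month interviews. Each contains one affected item among four prompts. How often a mother would agree merely because she was prompted is not given in the documents and cannot be derived from them.

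**The case against.** The case for leaving the scripts alone has several parts.

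*Referring back is a legitimate way to ask about change.* The wording is tentative, it says that time has passed, and a semi-structured format lets the interviewer probe a bare yes or no. This stands as a defence of feeding back the earlier answer at some point. It does not defend doing so before the mother has been asked openly.

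*Section 4.7 is not contradicted.* A reader might infer that the section promises the full set of questions in both rounds. It describes what the tool as a whole will elicit, and the first round does elicit it. This objection stands: dropping the question on what was least helpful is a missed opportunity, not a breach of the stated aim.

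*The second round still carries information.* A reader might infer that it cannot show what mothers value at six months. That goes too far. Mothers can disagree, and three of the four prompts in each script leave the earlier answer out.

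*The control item is different in kind.* Control mothers had no programme components to rank, so any consequence for what to keep in a programme arises only from Appendix 7. This is correct.

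*The interviewer.* A reader might infer that each mother is interviewed by the person who recruited and allocated her. The interviewer is the unblinded first research assistant, who has that role on weekdays. Under sections 4.4 and 5.4, however, attending physicians enrol some weekend families. The inference holds for many mothers but not for all.

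*No formal comparison of rounds is planned.* Section 5.3 claims neither stability nor confirmation. This is true and limits the harm to how the themes might be read.

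*Transcript checking.* Section 5.3 lets each mother verify her transcript, without saying when. If that happens before the second interview, an open question would not be wholly free of the first round. It would still be less leading than the present item.

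**Conclusion.** The point holds in a limited form. In Appendix 7 the only six-month item on helpfulness is leading and closed, comes before any open question, and omits what was least helpful. Agreement on it cannot be separated from acquiescence, and X depends partly on the interviewer. Appendix 8 has the same form for feelings about breastfeeding skills.

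The scope is one of four prompts per script, among the 20 mothers sampled in each arm. It would be wrong to count all 40 six-month interviews as compromised. The primary outcome, its test and the sample size are unaffected.

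That prompted mothers will tend to agree is a reasonable expectation about leading questions. The documents neither show it nor give its size. The conclusion also assumes that the scripts are used in the order written. An interviewer who probes openly first would lessen the problem, but nothing in the scripts asks for that. This is a cheap improvement, not an error in the trial's main design.

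**What to change.** Change the order in both six-month scripts.

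- **Appendix 7:** ask first, without prompting, which parts of the support the mother now finds, looking back, to have been most helpful and which least helpful. Record the answer. Then tell her what she said in the first round, giving both components if she named two, and explore any difference.
- **Appendix 8:** ask first how confident she feels, or felt before she stopped, about breastfeeding. Record the answer, then refer to the earlier one and explore any difference.

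This keeps the intended look at change over time and makes agreement informative, because the mother gives her current view before she is reminded of the old one. The other three prompts in each script can stay as they are.

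The cost is one or two added lines per script, made before the interviews begin, and a minute or two more per call. Over 40 calls that is 40 × 1 = 40 to 40 × 2 = 80 minutes of interview time in total.
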